**Methods:**

The quasi-experimental, noninferiority study will take place in public sector facilities in Kaduna and Ondo States. In each state, we will select 60 facilities, and from these, we will select a total of 30 nurses and midwives and 30 CHEWs to participate. Selected providers will be trained to provide implant services. Once trained, providers will recruit a minimum of 8125 women aged between 18 and 49 years who request and are eligible for an implant, following comprehensive family planning counseling. During implant insertion, providers will record data about the process and any adverse events, and 14 days post insertion, providers will ask 4410 clients about adverse events arising from the implant. Supervisors will observe 792 implant insertions to assess service provision quality and ask clients about their satisfaction with the procedure. We will conclude noninferiority if the CI for the difference in the proportion of adverse events between CHEWs and nurses and midwives on the day of insertion or 14 days post insertion lies to the right of −2%.

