### Sample Size

#### Day of Insertion

Calculation of the number of participants required for the study is based on the primary outcome—the frequency of adverse events associated with insertion on the day of the procedure.

Studies documenting adverse events of implant insertion on the day of procedure have found them to be rare. For example, a randomized clinical trial of 2008 women found that 0.2% clients using Jadelle and 0.8% clients using Implanon Classic experienced complications at insertion [26].

To detect a difference in proportion of adverse events between the 2 study arms with a noninferiority limit of 0.5%, 80% power, and 95% confidence level on the day of implant insertion, we would require a sample size of 2462 in each study arm, giving a total sample size of 4924. To account for possible clustering, we will include a design effect of 1.5, increasing the sample size to 7386. To allow for incomplete records, we will increase this by 10% to a total sample size of 8125.

We estimate that each provider will receive approximately 10 insertion clients per month and that we may see a refusal rate of 20%. With a total of 120 providers, we expect to recruit 1200 clients per month. We would therefore need to recruit clients for approximately 7 months to achieve the required sample size for insertions.

#### By Day 14

We expect the number of adverse events observed by day 14 to be higher than that at day 0 as we may start to see infections. This reduces the required sample size needed to detect a difference between health care provider types. To detect a difference in proportion of adverse events between the 2 study arms with a noninferiority limit of 1%, 80% power, and 95% confidence level 14 days after implant insertion, we would require a sample size of 1225 in each study arm, giving a total sample size of 2450. To account for possible clustering, we will include a design effect of 1.5, making the size 3675. Assuming 20% loss to follow-up makes a total sample size of 4410. If we expect to recruit 1200 clients per month, it will take around 4 months to recruit the sample size we require.

All recruited clients will be asked to return to the inserting provider for a follow-up visit at 14 days post insertion until the sample size of 4410 is reached.

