### Data Analysis

Quantitative data will be analyzed using statistical software Stata, version 13 (Stata Corp. College Station, Texas). Complete case analysis will be conducted. For safety monitoring, complication rates by provider will be generated by the study manager in Abuja every 3 months, to identify any providers with unusually high complication rates. These data will be checked and response activities will be agreed at the 3 monthly technical advisory committee meetings to be held in Abuja, which will be attended by staff from MSION and MSI, and ministry of health officials.

Training and supervision data will be presented using descriptive statistics. Insertion adverse events of CHEWs will be compared for noninferiority against the complication rates of nurses and midwives. To assess the equivalence between the nurses and midwives and the CHEWs, the risk difference between the 2 provider types together with their 95% CI will be derived by use of a generalized estimating equation model to adjust for clustering. If the CI of the risk difference between the 2 groups falls within the predetermined margin of equivalence (–2% to 2%, which is equivalent of lower bound of one side 97.5% CI), the 2 types of service providers can be considered equivalent.

Sensitivity analysis will be designed to control for group assignment bias among the 2 states. They will be analyzed both separately and together to identify any differences in performance between CHEWs in the northern state compared with the southern state.

All quality and acceptability indicators will be weighted equally, except for those most critical (infection prevention, correct clinical technique, and advice on where to go in case of problems), which will be given a higher weight. The difference in mean quality and acceptability scores between CHEWs and midwives will be compared using a *t* test.

Analysis of qualitative data will be undertaken manually or using a qualitative analysis software such as N-Vivo. Quotations will be labeled by cadre of speaker, and a thematic analysis will be carried out. Transcripts will be read and reread. Extracts will be coded according to themes and subthemes that emerge from the data or that have been identified before the analysis such as those included in the in-depth interview guide. A selection of quotes representing different cadres and views will be used to write a report structured around these themes.

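### Noninferiority is judged against 2 percentage points, but the study was sized on margins of 0.5 points (day 0) and 1 point (day 14), and nothing reconciles them

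*Protocol article*

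**What the plan says.** Under Sample Size, Day of Insertion, the calculation rests on "the frequency of adverse events associated with insertion on the day of the procedure" and is made "with a noninferiority limit of 0.5%, 80% power, and 95% confidence level on the day of implant insertion". The result is a "sample size of 2462 in each study arm, giving a total sample size of 4924". A design effect of 1.5 raises this to 7386, and 10% for incomplete records to 8125.

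Under By Day 14, the calculation is made "with a noninferiority limit of 1%, 80% power, and 95% confidence level 14 days after implant insertion". It gives 1225 per arm, 2450 in total, 3675 after the design effect and 4410 after 20% loss to follow-up.

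The decision rule uses another figure. The Methods paragraph of the Abstract concludes noninferiority if the CI on the day of insertion or "14 days post insertion lies to the right of" −2%. Data Analysis derives a 95% CI for the risk difference from a GEE model and concludes equivalence "If the CI of the risk difference between the 2 groups falls within the predetermined margin of equivalence", stated as –2% to 2%. Data Analysis names no time point; only the Abstract says explicitly that 2% serves both.

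**The concern.** The margin is the largest excess of adverse events the study is prepared to call acceptable, so it defines the claim. Here one document holds two answers for its primary objective, safety. The 2% figure appears nowhere in the Sample Size section, and the 0.5% and 1% figures appear nowhere in the decision rule. Data Analysis nevertheless calls 2% predetermined.

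Two points is also large beside the event itself. The only day-0 rates the protocol cites are "0.2% clients using Jadelle and 0.8% clients using Implanon Classic experienced complications at insertion", so 2 points is 2.5 to 10 times those rates. A conclusion of noninferiority could then cover an excess that the study's own sizing treats as the limit or beyond it, in a study whose results are meant to inform task-sharing policy.

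**Working it through.** **Inputs.** From Sample Size: margins 0.5 and 1 point, power 80%, 2462 and 1225 per arm, cited day-0 rates 0.2% and 0.8%. From the Abstract and Data Analysis: margin 2 points, 95% CI. Assumed, because not stated: planning rates of 0.5% (day 0, the midpoint of the two cited rates) and 1% (day 14), both back-solved from the stated sizes.

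**1. Reproducing the plan's sizes.** With equal rates p in both arms, n per arm = 2p(1−p)(z₁₋α + z₀.₈)² / m².

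- Day 0, p = 0.5%, m = 0.5%, one-sided 5%: 0.00995 × 6.1826 / 0.000025 = 2460.7, so 2461 (stated 2462).
- Day 14, p = 1%, m = 1%, one-sided 5%: 0.0198 × 6.1826 / 0.0001 = 1224.1, so 1225 (stated 1225).
- One-sided 2.5% gives 3124 and 1555, which does not match.
- The inflation steps match: 4924 × 1.5 = 7386, × 1.1 = 8125; 2450 × 1.5 = 3675, × 1.2 = 4410.

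**2. Could 2% have produced them?** At the same rates with m = 2%, n is 154 (day 0) and 307 (day 14) at one-sided 5%, or 196 and 389 at one-sided 2.5%. To get 2462 from a 2-point margin at one-sided 5%, p(1−p) would have to be 2462 × 0.0004 / (2 × 6.1826) = 0.0796, that is p of about 8.7%, far above the cited rates.

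**3. Chance of passing each margin.** P(pass) = Φ((m − d)/SE − 1.96), where d is CHEW minus nurse/midwife and SE = √[(p_N(1−p_N) + p_C(1−p_C))/n]. The n is the size per arm before inflation, that is, the effective size once the design effect and the allowance for incomplete records have been spent.

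Day 0, n = 2462, excess d exactly 0.5 points:

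| Nurse/midwife | CHEW | SE | (2% − d)/SE − 1.96 | Passes at 2% | Passes at 0.5% |
|---|---|---|---|---|---|
| 0.2% | 0.7% | 0.00191 | 5.91 | >99.9% | 2.5% |
| 0.5% | 1.0% | 0.00246 | 4.14 | >99.9% | 2.5% |
| 0.8% | 1.3% | 0.00290 | 3.20 | >99.9% | 2.5% |

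Day 14, n = 1225, 1% against 2%: SE = 0.00491; 0.01/0.00491 − 1.96 = 0.08, so 53% pass at 2%. At a 1-point margin d equals m and 2.5% pass.

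**4. Larger relative harms at day 0 under the 2% rule.** A tripling passes about 100% of the time at a base of 0.2%, 94% at 0.5% and 20% at 0.8%. At the 0.5% base, binomial simulation gave 93%, and simulation with 60 providers per arm and a design effect of 1.5 gave 92%.

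**5. Power if the sizing margins are applied with the 95% CI.** With no true difference: day 0, SE = 0.00201, 0.005/0.00201 − 1.96 = 0.53, power 70%; day 14, SE = 0.00402, 0.01/0.00402 − 1.96 = 0.53, power 70%. The shortfall from 80% arises because sizing used one-sided 5% and the 95% CI is one-sided 2.5%.

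**The case against.** A reader might infer that a tripling of day-0 adverse events would usually be declared noninferior. The document does not support that as a general statement. It holds near a 0.5% base rate, which is not stated, and fails at 0.8%, the upper rate the protocol itself cites. Table 2 counts unsuccessful insertion attempts and bleeding around the injection area on day 0, so a base rate above 0.5% cannot be excluded.

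A second objection is that the document justifies neither margin. That the smaller ones produced the sample size shows inconsistency, not that they are the acceptable limits. This stands in part: if 2% was fixed and justified before data were seen, the sponsor can show it. But nothing in the article supports 2%, whereas the smaller margins carry the whole sample size.

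Third, the conflict cannot be cured by swapping a number. The Abstract states a lower limit without saying which group is subtracted from which, and Data Analysis states a two-sided range; putting +0.5 into the Abstract's wording would reverse its meaning. This stands, and the fix must state the direction.

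Fourth, recruitment ended in December 2016 and cleaning is complete. That does not remove the conflict, since the margin is applied at analysis, but it makes disclosure part of the remedy.

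**Conclusion.** The decision rule contradicts the sample size, and this must be fixed. The contradiction itself needs no assumed rate: 2 points against 0.5 and 1. Its effect at day 0 is stable across the cited rates of 0.2% to 0.8%: an excess equal to the sizing margin passes more than 99.9% of the time instead of 2.5%. The day-14 figure, about 53% instead of 2.5%, rests on a back-solved base rate of 1%. All pass rates use the normal approximation and take the planned design effect as correct. Statements about a tripling should be given only with their range (about 100%, 94% and 20% at base rates of 0.2%, 0.5% and 0.8%).

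**What to change.** In the Abstract and in Data Analysis, replace the 2% rule by the sizing margins with the direction written out: define the risk difference as CHEW minus nurse/midwife, and conclude noninferiority if the upper 95% limit is below +0.5 percentage points at day 0 and below +1 percentage point by day 14. State which margin was fixed before data were seen, and if 2% was prespecified, show the CI against 2% as well.

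The cost is lower power. Under the 95% CI it is about 70% at both times by formula, and the article should say so in place of 80%. Keeping a two-sided range at the smaller margin would cost more: in binomial simulation at day 0 (0.5% in both arms, 2462 per arm), both limits fell inside ±0.5 points only about 40% of the time. No extra clients or data are needed, but because the data are already clean, the change must be reported openly as one made at the analysis stage.

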### Site and Provider Selection

The study will take place in public sector facilities in 2 Nigerian states, 1 in the north (Kaduna) and 1 in the south (Ondo). The north and south of Nigeria differ in religious beliefs, contraceptive prevalence rate, and availability of health care providers, making it necessary to generate evidence in each context. We will purposively select local government areas (LGAs) in Kaduna and Ondo States for study participation by excluding LGAs with overlapping interventions and, given the extensive supervision needs of the study, hard-to-reach LGAs.

Facilities will be eligible if they provide referral services on site or are located within 20 km of a referral facility, in case of adverse events resulting in the need to refer clients; if there is a provider interested in participating in the study who expects to be in the facility for the 12-month period of client recruitment; and if the facility has been providing FP in the previous 3 years and does not currently provide implants. Larger urban centers staffed by nurses, midwives, and CHEWs and smaller rural health centers staffed by a nurse or midwife only will be eligible for inclusion.

A total of 60 facilities will be selected in each state from eligible facilities, yielding a total of 120 facilities. Where there are more than the required number of eligible facilities, simple random sampling will be used to select facilities for inclusion. At least 30 nurse or midwife-led facilities will be selected in each state to allow inclusion of 30 nurses and midwives in the study. The remaining 30 facilities will include as many CHEW-led facilities as possible. From each CHEW-led facility, 1 CHEW will be trained, and 1 nurse or midwife or 1 CHEW will be trained from each nurse or midwife-led facility. The providers trained will be the individuals responsible for providing FP services at their facility.

**Table 1 table1:** Details of implant brands to be included in the study.

Product	Composition	Labeled duration of use	Format
Jadelle	150 mg levonorgestrel, 2 rods	5 years	2 rods, separate disposable trocar
Implanon Classic	68 mg etonorgestrel, 1 rod	3 years	1 rod preloaded in trocar

**Table 2 table2:** Implant insertion adverse events to be recorded.

Description of adverse reaction		Day recorded relative to procedure
Anaphylactic reaction to the implant		0
Implant insertion unsuccessful on first or second attempt		0
Implant breaks		0

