## Results

In total, 12 LGAs were selected in Kaduna State and 23 in Ondo State. We trained 60 CHEWs and a total of 60 nurses and midwives (30 of each from each state) in September and October 2015, and recruitment took place between November 2015 and December 2016. Data cleaning is complete and analysis is being finalized. Results are expected in March 2018.

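### The state analysis is aimed at CHEWs in the north against CHEWs in the south, a contrast that does not net out state background; a cadre-by-state contrast would.

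*Protocol article*

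**What the plan says.** The main comparison in Data Analysis is between cadres: "the risk difference between the 2 provider types together with their 95% CI will be derived by use of a generalized estimating equation model". The next paragraph turns to the states. It opens with "Sensitivity analysis will be designed to control for group assignment bias among the 2 states" and says the states will be "analyzed both separately and together to identify any differences in performance between CHEWs in the northern state compared with the southern state".

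Site and Provider Selection gives the reason for having two states: "The north and south of Nigeria differ in religious beliefs, contraceptive prevalence rate, and availability of health care providers". From this the article concludes that evidence is needed in both settings. Results confirms that both cadres are present in equal numbers in each state: "We trained 60 CHEWs and a total of 60 nurses and midwives (30 of each from each state".

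The sample size section sizes only the overall cadre comparison. For day 0, "we would require a sample size of 2462 in each study arm, giving a total sample size of 4924". The state comparison has no figure of its own.

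**The concern.** The study is built on a standard-care comparator: CHEWs are judged against nurses and midwives. The stated aim of the state analysis leaves that comparator out. A difference in event rates between northern and southern CHEWs has two possible sources: something about the states that affects every provider, or a difference in how CHEWs perform relative to the other cadre. The first says nothing about task-sharing. Only the second is evidence that CHEW provision works better in one setting than in the other.

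There is also a lesser concern. If each state is analysed separately and each receives its own noninferiority verdict, a pass in one and a miss in the other may be read as a state difference. It can arise by chance, because each state holds about half the clients.

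What is at stake is the interpretation of a sensitivity analysis, not the main result. It still deserves care, because evidence in each setting is a stated reason for the two-state design.

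**Working it through.** **Inputs.** From Sample Size: 2462 per arm at day 0 (margin 0.5%), 1225 per arm at day 14 (margin 1%), 80% power, design effect 1.5, totals of 7386 and 3675 after that inflation. From Data Analysis: 95% CI and margin of 2%. From Results: equal numbers of each cadre in each state. The planning event rates are not stated.

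**Reproducing the plan's figures.** With equal risk p in both arms, n = (z_alpha + z_beta)² × 2p(1−p) / margin².
- Day 0, p = 0.5%, margin 0.5%, one-sided 5%: n = 2461 (stated 2462).
- Day 14, p = 1%, margin 1%, one-sided 5%: n = 1225 (stated 1225).

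So 0.5% and 1% serve below as the implied planning rates. They are not the only possibility: with one-sided 2.5%, rates of about 0.4% and 0.8% come close to the stated sizes.

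**Effective size per cadre per state** (equal split assumed).
- Day 0: 7386 / 1.5 / 4 = 1231.
- Day 14: 3675 / 1.5 / 4 = 612.5.

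**Step 1: CHEW-only comparison when only the state matters.** Both cadres have risk p1 in one state and p2 in the other. SE = √{[p1(1−p1) + p2(1−p2)] / n}; rejection = Φ(d/SE − 1.96) + Φ(−d/SE − 1.96), with d = |p1 − p2|.

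| Assumed state rates | n | d (points) | SE (points) | d/SE | Rejects |
|---|---|---|---|---|---|
| 0.4% v 0.6%, day 0 | 1231 | 0.2 | 0.284 | 0.70 | 11% |
| 0.5% v 1.0%, day 0 | 1231 | 0.5 | 0.348 | 1.44 | 30% |
| 0.2% v 0.8%, day 0 | 1231 | 0.6 | 0.284 | 2.11 | 56% |
| 1% v 2%, day 14 | 612.5 | 1.0 | 0.694 | 1.44 | 30% |

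In every row the cadre difference is zero in both states. The contrast (CHEW minus nurse/midwife in one state) minus (the same in the other) is therefore zero. A binomial simulation of 200,000 runs, with states at 0.2% v 0.8% (day 0) and 0.4% v 1.6% (day 14), had a test of that contrast rejecting about 5% of the time, against 56–57% for the CHEW-only test. Step 1 does not depend on any noninferiority margin.

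**Step 2: separate state verdicts when nothing differs.** Per-state SE = √{2p(1−p)/n}; power = Φ(margin/SE − 1.96); chance of opposite verdicts = 2 × power × (1 − power).

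| Setting | SE (points) | Power per state | Opposite verdicts |
|---|---|---|---|
| Day 0, p 0.5%, margin 2% | 0.284 | about 100% | about 0% |
| Day 14, p 1%, margin 2% | 0.569 | 94% | 11% |
| Day 14, p 2%, margin 2% | 0.800 | 71% | 42% |
| Day 14, p 3%, margin 2% | 0.975 | 54% | 50% |
| Day 0, p 0.5%, margin 0.5% | 0.284 | 42% | 49% |
| Day 14, p 1%, margin 1% | 0.569 | 42% | 49% |

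The last two rows use the sizing margins, not the margin named for analysis.

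**Step 3: precision of the better contrast.** Its SE is √2 times the per-state SE, which is twice the SE of the overall risk difference.
- Day 0: √2 × 0.284 = 0.40 points; 95% CI about ±0.8 points.
- Day 14: √2 × 0.569 = 0.80 points; 95% CI about ±1.6 points.
- Power to detect a contrast as large as the sizing margin (0.5 or 1 point) is 24% at each time.

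**The case against.** The strongest reply is that the article commits to less than a critic might suppose. It says the sensitivity analysis is still to be designed, and that the states are analysed separately and together. Coming straight after the GEE paragraph, this most naturally means that the cadre risk difference is repeated by state and pooled. Separate analyses would then already use each state's own nurses and midwives, and a pooled model could hold an interaction. Whether it does is the sort of detail an unseen analysis plan may settle.

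Much of this stands. A reader might infer that the protocol prescribes a CHEW-only significance test, or a rule that a pass in one state and a miss in the other shows a difference. It states neither, so the percentages above describe what could follow from a literal reading and are not properties of a stated test. A reader might also infer that separate verdicts disagree about half the time. At the 2% analysis margin that is not so, unless day-14 rates are well above the implied 1%.

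The assumed rates also need care. The 0.2% and 0.8% are the article's figures for two implant brands, borrowed here as state rates, and nothing in the article shows that states differ that much. Events are few as well: at 0.5% v 1.0% there are about 6 and 12 effective events. An exact test would lower the day-0 rejection from 30% to 22%, and from 11% to 6% for the mildest gap.

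What does not fall is the target. The article states what the analysis is meant to identify, and that is a difference between CHEWs in two states it describes as different. An unseen interaction term would not change this stated aim.

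**Conclusion.** The point holds in a limited form. The stated aim of the state analysis does not separate cadre performance from state background, although the design supplies the comparator needed to do so. Under assumed state gaps and no cadre difference, a CHEW-only comparison at day 0 would signal a difference in roughly 11% to 56% of studies (30% in the middle case). Disagreement between state verdicts is secondary: negligible at day 0 and about 11% at day 14 with the 2% margin and a 1% rate.

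These figures assume an equal split by state and cadre, a design effect of 1.5, the implied planning rates of 0.5% and 1%, and illustrative state rates.

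It would be going too far to infer that the noninferiority result is compromised. This is a sensitivity analysis, no listed objective concerns a state difference, and the primary conclusion rests on the overall comparison.

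**What to change.** Replace the sentence on the state analysis with wording such as: Heterogeneity between states will be explored by adding state and a cadre-by-state term to the GEE risk-difference model. We will report the CHEW minus nurse/midwife risk difference in each state, and the difference between the two with its 95% CI. CHEW event rates by state will be descriptive. A state difference will not be inferred from those rates alone, or from one state meeting the margin and the other not.

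The cost is one reworded sentence and two model terms on data already collected; the article says the analysis was still being finalized. The result should be labelled exploratory. With an interval of about ±0.8 points at day 0 and ±1.6 at day 14, the report may have to say that a state difference can be neither shown nor excluded.
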